### 2.5. Outcome Measures

The outcome measures of this study are designed to evaluate the biomechanical differences in upper limb function during two propulsion modes: forward (push) and backward (pull). These include both kinematic and muscle activation variables.

Kinematic variables comprise joint angles, range of motion (ROM), and stroke trajectories, with a particular focus on the shoulder and elbow during the propulsion cycle.

Muscle activity will be evaluated using surface electromyography (sEMG), focusing on activation intensity and timing of the upper limb muscles involved in propulsion. Normalized iEMG and RMS values will serve as the primary metrics for inter-condition comparison. All EMG data are normalized to MVC, which is measured post-trial.

### 2.6. Procedures

Kinematic data will be collected using a VICON motion capture system (Oxford, UK) equipped with 10 fixed cameras. Reflective markers will be placed on anatomical landmarks of the shoulder, elbow, wrist, and hand to capture movement during each propulsion cycle. The recorded data will be processed with Visual 3D software (C-Motion, Germantown, MD, USA) to extract joint angles, ROM, and stroke trajectories. Sampling will be conducted at 100 Hz, and all signals will be low-pass filtered before analysis.

sEMG signals will be recorded using a Trigno Wireless EMG system (Delsys Inc., Natick, MA, USA) from ten upper limb muscles on the dominant side: anterior, middle, and posterior deltoid; biceps brachii; triceps brachii; pectoralis major; upper, middle, and lower trapezius; and latissimus dorsi. Surface electrodes will be positioned according to SENIAM guidelines, ensuring consistent and valid placement across participants. However, the SENIAM guidelines do not provide placement recommendations for the pectoralis major and latissimus dorsi muscles. For the pectoralis major, electrodes will be placed approximately one-third of the distance from the suprasternal notch to the anterior axillary line, following the method described by Król et al., (2007) [17]. For the latissimus dorsi, electrodes will be aligned parallel to the muscle fibers, approximately 4 cm below the inferior angle of the scapula, as validated in a previous study [18].

EMG signals will be sampled at 2000 Hz and processed through bandpass filtering (20–450 Hz), full-wave rectification, and smoothing using a root mean square (RMS) algorithm with a 100 ms moving window. Both integrated EMG (iEMG) and RMS values will be calculated to provide complementary insights: iEMG will reflect the cumulative muscle activity over time, while RMS will highlight instantaneous variations in muscle activation.

Maximum voluntary contractions (MVCs) will be measured post-trial and will be used to normalize all EMG signals for comparability. Although MVCs are commonly performed before experimental tasks, in this study, they will be conducted after the propulsion trials to prevent anticipatory muscle activation or learning effects that may influence natural propulsion patterns. Participants will be given a sufficient rest period after the trials to mitigate any fatigue effects before performing MVCs. For each muscle, MVC signals will be collected in three separate trials, each lasting 5 s, with 1-min rest intervals between trials to avoid fatigue. Participants will be seated in their manual wheelchairs, with their trunks supported and their arms positioned as needed for each targeted muscle. Verbal encouragement will be provided during each trial to help participants exert their maximum effort.

-For the deltoid (anterior, middle, posterior), participants will perform isometric shoulder flexion, abduction, and horizontal extension against resistance, respectively.-For the biceps brachii and triceps brachii, MVCs will be obtained during elbow flexion and extension against manual resistance at a 90° elbow angle.-For the pectoralis major, MVC will be performed via horizontal adduction against resistance with the arm abducted at 90°.-For the trapezius (upper, middle, lower), shoulder shrug, scapular retraction, and scapular depression will be tested, respectively, while sitting.-For the latissimus dorsi, isometric shoulder extension will be performed against resistance with the arm extended backward.

Temporal synchronization between motion and EMG data will be achieved using a TTL signal transmitted via the motion system’s analog trigger module, ensuring signal alignment across both systems. Each participant will complete propulsion trials in both modes, and three successful propulsion cycles will be recorded per condition for analysis.

### 2.7. Data Analysis

All collected data will be analyzed using SPSS Statistics software (version 26.0, IBM Corp., Armonk, NY, USA). Descriptive statistics (mean ± standard deviation) will be used to summarize participant characteristics and all outcome measures.

To assess the normality of the data distribution, the Shapiro–Wilk test will be conducted. Based on these results, either parametric or non-parametric tests will be used. For normally distributed data, repeated-measures analysis of variance (ANOVA) will be conducted to compare biomechanical parameters (e.g., joint angles, ROM, iEMG, RMS values) between the two propulsion modes (push vs. pull). Mauchly’s test will be performed to assess the assumption of sphericity, and if violated, the Greenhouse–Geisser correction will be applied. Signals will be sampled at 2000 Hz.

For non-normally distributed variables, the Wilcoxon signed-rank test will be applied. All statistical analyses will adopt a two-tailed significance level of *p* < 0.05. To assess the magnitude of differences between conditions, effect sizes will be reported (Cohen’s d or partial eta squared, as appropriate).

Additionally, kinematic variables such as shoulder flexion and extension angles, as well as stroke cadence, will be calculated over complete propulsion cycles. EMG signals will be band-pass filtered (20–450 Hz), full-wave rectified, and smoothed using the root mean square (RMS) method with a 100-ms moving window. Integrated EMG (iEMG) data will also be computed to capture the total muscle activation over each propulsion cycle. EMG data will be normalized to maximum voluntary contraction (%MVC). Comparisons of muscle activity patterns will be made across propulsion modes to evaluate biomechanical efficiency, with a focus on reduced activation in shoulder prime movers during the pull phase.

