## 2. Materials and Methods

### 2.1. Participants

A total of 30 adults diagnosed with SCI will be recruited for this study. The inclusion criteria will be as follows: participants will be adults between the ages of 20 and 60 years who will have been diagnosed with spinal cord injury (SCI). They must have used a manual wheelchair regularly for at least six months and will be required to have the ability to propel a wheelchair independently over a 10-m track. Additionally, participants must not have any acute or chronic impairments affecting their upper limbs and will need to provide written informed consent before participation.

The exclusion criteria will be defined as follows: individuals will be excluded if they have neurological conditions other than SCI, current upper limb fractures, clinically diagnosed shoulder pathology, or other musculoskeletal disorders that could interfere with propulsion. Further exclusion criteria will include active shoulder pain, cognitive impairments that limit comprehension of study instructions, and prior participation in competitive wheelchair sports or structured upper limb training programs within the past six months. Any additional medical condition identified by the research team as potentially compromising participant safety or data integrity will also result in exclusion.

Before enrollment, all participants will receive detailed information about the study’s purpose, procedures, risks, and benefits, and written informed consent will be obtained.

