### 2.2. Study Design

This study will employ a repeated-measures within-subject design to evaluate the usability and biomechanical effects of a detachable push–pull dual-propulsion device developed for manual wheelchair users. Each participant will perform wheelchair propulsion tasks under two specific experimental conditions: (1) forward propulsion using the traditional handrim method (standard manual wheelchair), and (2) backward propulsion using the dual-propulsion device (pull mode). To enhance clarity, a schematic illustration (Figure 1) will be provided to visually depict the two experimental conditions: push propulsion using a handrim and pull propulsion using the dual-propulsion device. The arrows in the figure will indicate the direction of propulsion and the rotation of the wheels.

These two propulsion strategies will be selected to distinguish the mechanical and physiological differences between conventional pushing and the novel pulling movements using the developed device. This within-subject comparison will enable the evaluation of the dual-propulsion system in relation to standard propulsion, with a focus on biomechanics and usability.

While this study will adopt a within-subject repeated-measures design to compare two propulsion modes, we acknowledge the absence of a separate control group as a limitation. In future randomized controlled trials, we plan to include a conventional propulsion-only control group to improve external validity and control for potential confounding variables.

The order of propulsion conditions will be randomized for each participant to minimize potential learning effects, fatigue accumulation, and sequence bias. Prior to data collection, all participants will receive standardized instructions and practice sessions on the use of the propulsion device and experimental procedures to ensure sufficient familiarity.

All experiments will be conducted in a controlled laboratory setting. The primary outcome measures will include kinematic data obtained from 3D motion analysis and electromyographic (EMG) signals collected from upper limb muscles. Adequate rest intervals will be provided between conditions to prevent muscular fatigue and maintain the accuracy of the data.

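### A normality pre-test picks the analysis variable by variable, so what is tested for the EMG metrics is not fixed in advance, and the randomised order is left unused

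*Protocol article*

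**What the plan says.** Section 2.7 (Data Analysis) sets out the whole rule. It begins with a pre-test: "To assess the normality of the data distribution, the Shapiro–Wilk test will be conducted". It continues: "Based on these results, either parametric or non-parametric tests will be used". Variables judged normal go to repeated-measures ANOVA comparing push with pull. For the rest: "For non-normally distributed variables, the Wilcoxon signed-rank test will be applied". The Discussion and the Conclusions repeat that the data distribution will decide between parametric and non-parametric analysis.

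For the ANOVA branch, Mauchly's "test will be performed to assess the assumption of sphericity", with Greenhouse–Geisser as the correction. Mode is the only within-subject factor named, and it has two levels.

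On order, Section 2.2 states: "The order of propulsion conditions will be randomized for each participant to minimize potential learning effects, fatigue accumulation, and sequence bias". Section 2.4 says the same. Section 2.7 names no period, sequence or order term. Table 1 shows push trials at T2, rest at T3 and pull trials at T4.

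Section 2.5 makes normalised iEMG and RMS the primary metrics, and Section 2.6 lists ten muscles. The hypothesis at the end of Section 2.2 is that pull mode gives a better balance of activation across upper-limb muscles and less shoulder loading.

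**The concern.** Three features of the stated analysis do not fit a two-mode, randomised-order design.

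- **The gate.** The paired t-test concerns the mean difference; the signed-rank test concerns the location of a symmetric distribution of differences. Letting a pre-test choose means that the question asked of each muscle depends on the sample. A claim about balance is a comparison across muscles, and it is hard to read if some are summarised by a mean difference and others by a rank statistic. The text also does not say what is tested for normality: raw values in each mode, paired differences or residuals. Only the last two matter for a paired analysis.
- **The order.** The authors randomise order because they expect learning and fatigue. Any such effect then stays in the error term, since the ANOVA as described has no term for it and Wilcoxon cannot carry one.
- **Sphericity.** The check has no content when there are only two modes.

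**Working it through.** **Inputs from the protocol.** n: "A total of 30 adults diagnosed with SCI will be recruited for this study". Alpha is 0.05, two-sided (Section 2.7). Modes: 2. EMG variables: 10 muscles × 2 metrics = at least 20. The article gives no effect size, SD or power, so there is no figure of its own to reproduce. All effect sizes and distribution shapes below are assumptions.

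**1. Sphericity.** Mauchly's df = k(k−1)/2 − 1. For k = 2: 2×1/2 − 1 = 0. For k = 3: 3×2/2 − 1 = 2. With k = 2 there is one contrast, so W = 1 and epsilon = 1 for any data. There is no p-value, and the correction never acts. On a simulated dataset the two-level ANOVA gave F = 1.0955, equal to the squared paired t.

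**2. Error rate of the gate.** Simulation of paired differences, n = 30, 10,000 runs, type I error for a mean difference of zero:

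| True differences | t | Wilcoxon | Gated choice | Sent to Wilcoxon |
|---|---|---|---|---|
| Normal | 5.0% | 4.9% | 5.1% | 5% |
| t with 3 df | 4.3% | 5.1% | 5.1% | 46% |
| Skewed log-normal (sigma 0.6), mean zero | 7.5% | 15.2% | 15.0% | 84% |

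For symmetric differences the gate costs almost nothing in alpha. In the skewed case its 15.0% is Wilcoxon's own figure: most datasets are moved to a test that does not address the mean.

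**3. How often the gate would switch.** This depends on what is tested. Assuming log-normal EMG, within-person correlation 0.7 and n = 30, Shapiro–Wilk rejects as follows:

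| Between-person CV | Raw values, either mode | Raw paired differences |
|---|---|---|
| 40% | about 73% | about 21% |
| 60% | about 94% | about 41% |
| 80% | about 99% | about 59% |

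The undefined object of the test alone moves the switching rate from 21% to 73% at a CV of 40%. On the paired-difference reading the muscles would be divided between the two tests. On the raw-value reading at a high CV nearly all would go to Wilcoxon.

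**4. Order.** Let the paired difference have SD 1, and let order shift it by +0.5 or −0.5, with a 15/15 split. The mean difference is unbiased. Without an order term the expected sample variance is 1 + 0.25×30/29 = 1.26, so the standard error is inflated. With a mode effect of 0.53 SD:

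- With an order term: noncentrality 0.53×√30 = 2.90 on 28 df, power 80%.
- Without it, by simulation: 73% (78% if the order shift is 0.3 SD).

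A separate run at a mode effect of 0.55 SD gave 83%, 81%, 76% and 54% without the term for order shifts of 0, 0.3, 0.5 and 1.0 SD, against 82–83% with it. Type I error without the term fell to 4.2%, 2.7% and 0.7% at 0.3, 0.5 and 1.0 SD, so with a balanced split the unadjusted test is conservative.

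The balance of the two orders is not stated. Under simple randomisation, a split of 20:10 or worse has probability 9.9%.

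**5. If the Table 1 sequence were followed for everyone.** The estimate would carry the whole period effect. Type I error would be 35% at 0.3 SD and 75% at 0.5 SD, and no model could separate mode from period.

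**The case against.** The strongest defence is that a condensed article may leave an order term to an analysis plan that is not shown. Section 2.7 is silent on order; it does not assert that order has no effect. That stands, and it makes the order part the weakest of the three. The gate and the sphericity step are different: they are stated rules, and further detail elsewhere would not remove them from the text.

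Several stronger readings are tempting, and the document does not support them:

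- *The gate inflates the false-positive rate.* Not in general; it is about 5% for normal or symmetric differences.
- *Normality will be tested on raw values, so almost every EMG variable will fail.* The text does not say which values are tested, and gives nothing on the skewness of %MVC data.
- *At least one variable is likely to be switched by chance.* The figure 1 − 0.95^20 = 64% needs 20 variables that are all normal and independent. iEMG and RMS come from the same signal, so independence is implausible.
- *Ignoring order biases the comparison.* With randomised order and no carryover there is no average bias; the loss is power.
- *The void sphericity step invalidates the ANOVA.* It changes no result.
- *Cohen's d is assigned to Wilcoxon.* Section 2.7 leaves the effect size to be chosen as fits, so this cannot be held against it.

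**Conclusion.** The point holds in a limited form. The certain part is that the text makes the test for each primary EMG metric depend on the observed data, without defining what is tested for normality, and allows it to differ between muscles. The harm is to the definition and comparability of results; a general inflation of alpha is not shown. How often switching would occur cannot be known from the document. The range of 21% to 99% in the working rests on log-normality, a correlation of 0.7 and CVs of 40–80%.

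The order part is a loss of precision, from 80% to 73% power under the assumed 0.5 SD order effect, 0.53 SD mode effect and equal split. It would be smaller for a weaker order effect and absent if there were none. It becomes a question of bias only if the Table 1 sequence is what is actually done. The columns may be only a layout, but they conflict with Sections 2.2 and 2.4 as they stand.

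The sphericity step is void and harmless.

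**What to change.** 1. Remove the Shapiro–Wilk gate. Fix one paired analysis and one scale per outcome type in advance: log %MVC for EMG, reported as a pull/push ratio with 95% CI; untransformed values for joint angles and ROM.
2. Use one mean per participant per mode, with mode, period and sequence as fixed effects and a random participant effect. If individual trials (five per mode in Section 2.4) or cycles (three per condition in Section 2.6) enter the model, add a random participant-by-mode term. With a random participant effect alone, simulated type I error is about 11–33% for three to five trials per mode, assuming participant-by-mode variance of 0.25 to 1.0 times the trial variance. One mean per mode holds 5%.
3. Keep Wilcoxon on paired differences as a sensitivity analysis.
4. Delete Mauchly's test and Greenhouse–Geisser.
5. Reconcile Table 1 with the randomised order in Sections 2.2 and 2.4, and state whether the two orders are balanced.

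The cost is wording, settled before the data are analysed, and about one residual degree of freedom when one mean per mode is used. The named SPSS software can fit the model. No extra participants or measurements are needed.

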This study protocol was reviewed and approved by the Institutional Review Board of the National Rehabilitation Center (Approval No. NRC-2024-04-018). It was designed in accordance with the SPIRIT 2013 guidelines (Standard Protocol Items: Recommendations for Interventional Trials) [14]. A flowchart will illustrate the sequential steps of the experimental protocol (Figure 2), including participant recruitment, familiarization with the propulsion device, randomized push and pull trials along a 10-m track, and synchronized collection of kinematic and electromyographic (EMG) data. Maximum voluntary contraction (MVC) values will be recorded post-trial for EMG normalization.

The primary hypothesis of this study is that the pull-mode propulsion using the dual-propulsion device will result in more balanced upper limb muscle activation and reduced shoulder loading compared to standard push-mode propulsion.

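### Twenty unranked primary EMG comparisons, plus kinematics, share one 0.05 threshold, and no result is named as deciding the primary hypothesis

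*Protocol article*

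**What the plan says.** Section 2.2 (Study Design) sets the primary outcomes broadly: "The primary outcome measures will include kinematic data obtained from 3D motion analysis and electromyographic (EMG) signals collected from upper limb muscles". Its primary hypothesis is that pull mode "will result in more balanced upper limb muscle activation and reduced shoulder loading compared to standard push-mode propulsion". No muscle, metric or index is attached to either half of that statement.

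Section 2.5 (Outcome Measures) says of EMG: "Normalized iEMG and RMS values will serve as the primary metrics for inter-condition comparison". On movement it says: "Kinematic variables comprise joint angles, range of motion (ROM), and stroke trajectories, with a particular focus on the shoulder and elbow".

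Section 2.6 (Procedures) records EMG "from ten upper limb muscles on the dominant side" and lists them: three deltoid parts, biceps, triceps, pectoralis major, three trapezius parts and latissimus dorsi.

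Section 2.7 (Data Analysis) uses repeated-measures ANOVA, or the Wilcoxon signed-rank test for non-normal variables, to contrast push with pull on joint angles, ROM, iEMG and RMS. It adds stroke cadence to the variables to be calculated. On the threshold it says: "All statistical analyses will adopt a two-tailed significance level of" 0.05. Muscle activity is then to be compared "with a focus on reduced activation in shoulder prime movers during the pull phase"; the muscles meant are not listed.

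**The concern.** The plan has a primary hypothesis but no primary test. Two metrics on each of ten muscles, together with the kinematics, all carry primary status, and one threshold applies to each. Nothing says which result, or how many, would confirm the hypothesis, or which metric prevails if iEMG and RMS disagree. They can disagree: section 2.7 accumulates iEMG over each propulsion cycle, so cycle duration affects it.

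Two things are at stake. The chance of at least one significant result from a device with no effect is well above 5%. In addition, with the prime movers unlisted and balance undefined, a fall in one muscle or a rise in another could each be presented as support once the data are known. The article is written to confirm: it states a primary hypothesis, the Discussion speaks of confirming the expected benefits, and the Abstract says the findings will inform rehabilitation guidelines.

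**Working it through.** The article gives no familywise error rate or power, so there is no figure to reproduce.

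**Inputs from the article**
- Muscles: 10 (section 2.6).
- Primary EMG metrics per muscle: 2 (section 2.5).
- Threshold: two-tailed 0.05 (section 2.7), hence 0.025 in any one direction.
- Participants: 30, each measured in both modes (sections 2.1 and 2.2).

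**Assumed, because the article does not give them**
- Correlation between muscles, and between iEMG and RMS of one muscle.
- Number of kinematic variables: 6 to 10.

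**Step 1, count.** 10 muscles × 2 metrics = 20 primary EMG comparisons.

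**Step 2, independent tests, no true effect.**
- At least one false positive in either direction: 1 − 0.95^20 = 1 − 0.358 = 0.642. Expected number: 20 × 0.05 = 1.0.
- At least one in a single fixed direction: 1 − 0.975^20 = 1 − 0.603 = 0.397. Expected number: 20 × 0.025 = 0.5.

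**Step 3, metrics fully redundant (10 independent tests).**
- Either direction: 1 − 0.95^10 = 0.401.
- One direction: 1 − 0.975^10 = 0.224.

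**Step 4, correlated tests.** Simulated null trials with 20 paired t tests and n = 30 give these chances of at least one false positive in either direction:

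| Between-muscle correlation | iEMG–RMS correlation 0.8 | iEMG–RMS correlation 0.95 |
|---|---|---|
| 0.3 | 0.50 | 0.43 |
| 0.5 | 0.43 | 0.37 |
| 0.7 | 0.32 | 0.27 |

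A separate simulation (20,000 null trials per setting) used between-muscle correlations of 0 to 0.7 and metric correlations of 0 to 0.9. It gave 28–64% in either direction and 14–40% in one fixed direction. The upper ends are the independent case.

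**Step 5, kinematics added.** With 6 or 10 kinematic variables (mutual correlation 0.3, independent of EMG), the either-direction chance is 46–77%. The one-direction figure is 25–50%, but it means little here because the article gives the kinematic variables no favourable direction.

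**Step 6, a narrow family.** If only four prime movers counted (assumed), there would be 4 × 2 = 8 tests. Either direction: 1 − 0.95^8 = 0.337. One direction: 1 − 0.975^8 = 0.183.

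**Step 7, price of control.** With 30 pairs and 80% power (noncentral t), the detectable standardized paired difference is:
- 0.529 for one test at 0.05;
- 0.715 at 0.05/10 = 0.005, the strictest Holm step over ten muscles;
- 0.767 at 0.05/20 = 0.0025, Bonferroni over all 20.

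**The case against.** The strongest reply is that multiplicity detail usually sits in an analysis plan, and that section 2.7 never uses the word unadjusted. The count of 20 separate tests is also a reading. Section 2.7 invokes Mauchly's test, which has no role with two modes and might hint at muscle as a further within-subject factor. These points soften the finding but do not remove it. No multi-factor model is described, the stated contrast is push against pull, and the article itself names two primary metrics and fixes one threshold for every analysis.

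It is also fair to say that sections 2.2 and 2.5 need not contradict each other. The sentence in 2.5 stands in the EMG paragraph and can mean the main EMG metrics. What remains is the lack of ranking. Handrim pushing and lever pulling are different movements, so a null effect on every variable is a benchmark and not a forecast.

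A reader might infer four stronger claims that the article does not support:
- That a chance finding in the hoped-for direction is likely. A two-tailed 0.05 test spends only 0.025 on that side, so the 20 EMG tests reach at most about 40%. The figure passes 50% only from 28 independent tests (1 − 0.975^28 = 0.508).
- That a false-positive muscle is probable in any case. It exceeds 50% only near independence, which is unrealistic for two metrics from the same signal.
- That the authors expect trapezius and latissimus dorsi activation to rise with this device. Section 3 reports such rises from earlier reverse-propulsion studies; for this device it hypothesizes only a shift of workload.
- That increases would go unreported. Section 2.7 commits to descriptive statistics for all outcome measures, two-tailed tests and effect sizes.

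**Conclusion.** The point holds as a lack of hierarchy and error control among the primary comparisons. Followed as written, the plan carries a 64% chance of at least one false-positive EMG result if the 20 tests are independent. That falls to about 27–50% with between-muscle correlations of 0.3–0.7 and iEMG–RMS correlations of 0.8–0.95. For a single fixed direction the chance is up to about 40%, and 14–40% over the correlations examined. These figures assume no true effect on any EMG variable, one test per muscle and metric, and correlations that the article does not supply.

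Because balance is undefined and the prime movers are unnamed, either direction could be read as favourable. The practical risk therefore lies nearer the either-direction figures than the one-direction figures. The freedom to choose the supporting result afterwards matters as much as the error rate, and can be closed credibly only before the data are seen.

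**What to change.** Before any data are seen, amend sections 2.2, 2.5 and 2.7 in one of two ways:

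1. Name one primary EMG variable tied to the primary hypothesis and test it at 0.05. A prespecified RMS-based balance index with its muscles listed is one example. Such an index addresses only the balance half of the hypothesis, so the text should say what, if anything, addresses shoulder loading. The ten single-muscle comparisons of the same metric then form a Holm-adjusted secondary family.
2. Name one primary metric, iEMG or RMS, and apply Holm adjustment across its ten muscle comparisons as the primary family.

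In both cases, label the other metric and the kinematics exploratory and present them as estimates with 95% confidence intervals. List the shoulder prime movers, and interpret increases and decreases in all ten muscles alike.

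The cost is wording; no new measurement is needed. Single-muscle p-values become somewhat less favourable. The first option keeps the detectable difference for the primary test at about 0.53 standard deviations of the paired difference. Under the second, the strictest Holm step needs about 0.72.
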